# Effects of whole body vibration exercise on neuromuscular function for individuals with knee osteoarthritis: study protocol for a randomized controlled trial

**DOI:** 10.1186/s13063-017-2170-6

**Published:** 2017-09-20

**Keywords:** Neuromuscular function, Randomized controlled trial, Whole body vibration, Strength training, Knee osteoarthritis

## Abstract

**Background:**

Knee osteoarthritis (KOA) is a leading cause of public disability. Neuromuscular function contributes to the development and/or progression of KOA. Whole body vibration (WBV) exercise improve the neuromuscular function of patients with neurological disorders and even that of older patients with limited exercise options. Therefore, WBV exercise may offer an efficient and alternative treatment for individuals with KOA. However, the effects of WBV training on the neuromuscular function of individuals with KOA remain unclear. Therefore, this study attempts to investigate the effect of a 12-week WBV exercise on the neuromuscular function of individuals with KOA.

**Methods/design:**

We will conduct a prospective, single-blind randomized controlled trial on 180 KOA patients. Participants will be randomly assigned to the WBV exercise, lower extremity resistance training, and health education groups. The WBV exercise group will participate in a 12-week WBV training. The lower extremity resistance training group will undergo a 12-week lower extremity resistance training of both lower limbs. The control group will receive health education for 12 weeks. After the intervention, the participants will be followed up for 3 months with no active intervention. Primary outcome measures will include anthropometric measurements, gait analysis during walking and stair climbing, muscle strength test of the knee and ankle, proprioception test of the knee and ankle, and neuromuscular response of the leg muscles. Secondary outcome measures will include self-reported pain and physical functional capacity, and physical performance measures. Furthermore, adverse events will be recorded and analyzed. If any participant withdraws from the trial, intention-to-treat analysis will be performed.

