## Methods/design

### Study design

The study design is a prospective, single-blind randomized controlled trial. Three intervention programs, namely, a WBV exercise program, lower extremity RT, and a health education program, will be included in the study (Fig. 1). This study will be conducted at the Sport Medicine and Rehabilitation Center, Shanghai University of Sport. The power analysis with settings at *α* = 0.05, power (1 − *β*) = 0.80 and effect size = 0.25 showed that three groups of 120 participants in total was the required sample size. Given the dropouts, we decided to recruit 180 participants for the research. A total of 180 patients from community centers in Yangpu District, Shanghai, China will be included through advertisements placed in various community centers by the recruiter. A multidisciplinary team composed of clinicians, physiotherapists, and exercise specialists will run the program.

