#### Primary outcome measures

##### Anthropometric measurements

The body weight and height of each participant in minimal clothing and bare feet will be measured. Body height will be measured to the nearest 0.5 cm with a fixed stadiometer (Holtain Ltd., Crymych, Dyfed, UK). Body weight will be measured to the nearest 0.1 kg on a standard scale (TBF 543 model; Tanita, Tokyo, Japan). Body Mass Index will be calculated as follows:$$ \mathrm{Body}\  \mathrm{mass}\  \mathrm{in}\mathrm{dex}\kern0.5em =\kern0.5em \mathrm{Body}\  \mathrm{weight}\  \mathrm{in}\ \mathrm{kg}/{\left(\mathrm{Body}\  \mathrm{height}\  \mathrm{in}\ \mathrm{m}\right)}^2. $$

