##### Knee extensors and flexors strength

Knee extensor and flexor strength of the affected knee joint will be measured using an isokinetic dynamometer (850, Biodex, Shirley, NY, USA). The assessor will secure the participants to the device at the upper chest, pelvis, and distal femur on the tested side with Velcro straps. Three maximum concentric contractions for the knee extensors and flexors will be performed at an angular velocity of 90°/s. All data will be normalized by kilogram of body weight. The highest peak torque will be used for analysis. The dynamic endurance of the knee extensors and flexors will be assessed by measuring 40 repeated maximum isokinetic contractions at an angular velocity of 180°/s. The work of each contraction in the knee moving angle of 80°–10° will be recorded. The Endurance Index is defined as the ratio of the work performed during the last five contractions over the first five contractions.

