##### Neuromuscular response

Neuromuscular response, indicated by muscle latency, will be assessed using electromyography (EMG) of the leg muscles while an unexpected perturbation is applied to the ankle. A customized trapdoor with an 18° tilt angle will be used to generate an ankle inversion perturbation while the participants stand barefoot on the trap doors. The Noraxon EMG system (Noraxon USA Inc., Scottsdale, AZ, USA) will be used to collect surface EMG signals from five muscles (rectus femoris, semitendinosus, gastrocnemius, peroneus longus, and anterior tibialis) of the right leg and onset signals at the trapdoor tilting with a sampling frequency of 1000 Hz. Both feet will be randomly tilted at least seven times to decrease anticipatory effects. The onset latency of the muscles refers to the time interval in milliseconds (ms) between the trapdoor initiation and the first rising front of the EMG burst from the baseline. The EMG onset will be visually determined by an experienced researcher.

Furthermore, muscle activation will be determined during level walking and stair climbing. EMG data will be collected from eight lower extremity muscles in accordance with the recommended muscles for gait analysis from Winter and Yack [33]; these muscles are the ipsilateral and contralateral erector spinae at the level of the iliac crest, rectus femoris, vastus medialis, vastus medialis, tibialis anterior, biceps femoris, peroneus longus, and gastrocnemius. The Noraxon EMG system (Noraxon USA Inc., Scottsdale, AZ, USA) will be used to collect surface EMG signals from these muscles of the right leg with a sampling frequency of 1000 Hz. The EMG signals from five complete gait cycles per task will be used in data reduction. Prior to the EMG data collection, maximal isometric contraction data will be gathered for each muscle. The mean EMG amplitude and on-off muscle timing during a gait cycle will be used in the data analysis [34].

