### Statistical analysis

SPSS for Windows, version 17.0 (SPSS Inc., Chicago, IL, USA) will be used for statistical analysis. If any participant withdraws from the trial, the missing values will be replaced by the last assessment score of the participant. And all available data will be analyzed using an intention-to-treat analysis. Chi-squared tests will be used to test for demographic differences among the WBV training, RT, and control groups.

An intention-to-treat analysis will be performed by including all participants in the analysis according to the original group allocation. The follow-up will be maximized regardless of the program attendance. Repeated-measurement analysis of variance will be used to evaluate for between- and within-group difference. Bonferroni’s post hoc test will used for comparing the results. Data will be presented as the mean and standard deviation, and significance will be set at 0.05.

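### Five multi-variable batteries are all primary, with no lead variable, time point or contrast and no control of error across outcomes

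*Protocol article*

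**What the plan says.** The abstract (Methods/design) lists five batteries as primary: "Primary outcome measures will include anthropometric measurements, gait analysis during walking and stair climbing, muscle strength test of the knee and ankle", followed by proprioception of the knee and ankle and the neuromuscular response of the leg muscles. The Primary outcome measures section covers the same five, each with several variables:

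- **Anthropometry:** "The body weight and height of each participant in minimal clothing and bare feet will be measured", and BMI is calculated from them. The introduction to Outcome measures also counts BMI among the demographic information.
- **Gait:** kinematics and kinetics at two walking speeds and on stairs.
- **Strength:** "Knee extensor and flexor strength of the affected knee joint will be measured using an isokinetic dynamometer". Peak torque and an Endurance Index are defined. No ankle strength test is described.
- **Proprioception:** movement-detection thresholds at the knee and ankle.
- **Neuromuscular response:** onset latency in five muscles, and EMG of eight muscles during the gait tasks. For the latter, "The mean EMG amplitude and on-off muscle timing during a gait cycle will be used in the data analysis".

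Outcomes are assessed at baseline, 3 months and 6 months. The Background compares vibration exercise with both resistance training and health education. Under Statistical analysis, "Repeated-measurement analysis of variance will be used to evaluate for between- and within-group difference", a Bonferroni "post hoc test will used for comparing the results", and "significance will be set at 0.05". The Study design section gives one power statement: "effect size = 0.25 showed that three groups of 120 participants in total was the required sample size". It ties that effect size to no outcome.

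**The concern.** The trial asks whether vibration exercise improves neuromuscular function. As written, the plan spreads that question over five co-equal batteries and does not say which variable, visit or pair of arms carries the answer. The Bonferroni step follows an ANOVA and adjusts the comparisons made within one variable. Nothing in the text extends it to the set of variables.

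Two things are at stake. First, a claim based on the primary outcomes has no defined error rate. Second, the variable that is put forward can be chosen after the data are seen, and any choice would be consistent with the protocol. The list also contains items that cannot serve as efficacy endpoints. Adult height should hardly change over 12 weeks of exercise, so a group difference in it would mainly reflect chance imbalance at baseline. Finally, the sample size is justified for no identified primary variable.

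**Working it through.** **1. The plan's own figure.** Inputs from Study design: alpha 0.05, power 0.80, effect size 0.25 (type not named; read as Cohen's f), three groups, total 120. Equal allocation is assumed.

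- One-way ANOVA: noncentrality = f² × N = 0.0625 × 120 = 7.5, which gives power 67.6%. Power of 80% needs 158 (159 balanced), so this model does not reproduce 120.
- Between-group effect in a repeated-measures ANOVA: noncentrality = f² × N × m / (1 + (m − 1)ρ). With m = 2 measurements and ρ = 0.5 it is 0.0625 × 120 × 2 / 1.5 = 10, which gives power 80.5%. The required N is 119 (120 balanced), so this reproduces 120. The article states neither m nor ρ.

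The figure is thus reproducible for a single test at 0.05, under unstated settings.

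**2. Counting the variables from the Primary outcome measures section.**

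| Battery | Count |
|---|---|
| Height, weight, BMI | 3 |
| Peak torque and Endurance Index, knee extensors and flexors | 2 × 2 = 4 |
| Proprioception, 2 joints × 2 directions | 4 |
| Onset latency, 5 muscles | 5 |
| Gait EMG, 8 muscles × 2 measures × 3 tasks | 48 |
| Total | 64 |

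This is my count; the article gives none. It is 62 if one proprioception direction is used. It is 80 if stair ascent and descent are separate tasks (8 × 2 = 16 more). Joint kinematics and kinetics are left out because the article names no variables for them.

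**3. Chance of at least one false positive when no variable has a group effect.** For m independent tests at 0.05 it is 1 − 0.95^m:

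- m = 5 (one variable per battery): 1 − 0.774 = 22.6%
- m = 16 (the count without gait EMG): 1 − 0.440 = 56.0%
- m = 64: 1 − 0.0375 = 96.2%, with 64 × 0.05 = 3.2 false positives expected

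The variables are correlated, and the documents give no correlations, so a range is assumed. Simulating 2-df group tests (20,000 runs) on equally correlated outcomes gives:

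| Correlation | 5 tests | 64 tests |
|---|---|---|
| 0.1 | 23% | 95% |
| 0.3 | 21% | 86% |
| 0.5 | 19% | 67% |
| 0.8 | 13% | 34% |
| 0.9 | 10% | 21% |

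If the 64 variables are correlated only within each battery, the rate is 81% at 0.5 and 46% at 0.9.

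**4. What error control costs.** Under the model that reproduces 120, Bonferroni over five tests (0.05 / 5 = 0.01) lowers power at N = 120 from 80.5% to 59.2% and raises the required N to 174.

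Naming a two-arm contrast also changes power. With f = 0.25 over three arms, the widest pairwise difference is between 0.25 × 3/√2 = 0.53 SD (two means equal) and 0.25 × √6 = 0.61 SD (means equally spaced). A plain two-sample t test on that contrast gives:

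| Per arm | Alpha 0.05 | Alpha 0.05 / 4 = 0.0125 (first Holm step, four variables) |
|---|---|---|
| 40 | 65–77% | 43–57% |
| 60 | 82–91% | 64–79% |

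**The case against.** The strongest defence has four parts.

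- **No success rule is stated.** The article never says that one significant variable makes the trial positive, and the Discussion speaks of estimating an effect. This stands. The percentages are conditional on an any-one-wins reading, and the direct risk is selective emphasis.
- **The variables are correlated, and 64 is not a document figure.** This also stands. A reader might infer that a false positive primary result is nearly certain. That needs near-independent tests as well as the unstated success rule, and measures taken on one leg are unlikely to be independent. Nor is 64 a firm minimum: it includes height and the derived BMI, and one reading gives 62.
- **Some adjustment exists, and the visits need not multiply the tests.** Bonferroni is named, so the accurate description is unadjusted across outcomes. One repeated-measures ANOVA can cover all visits for a variable. A reader might infer that the two post-baseline visits inflate the error further, but the text does not establish this.
- **An article condenses, and an analysis plan may say more.** This does not rescue the point. The article states its primary outcomes rather than omitting them, and choosing the primary endpoint is a protocol decision.

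**Conclusion.** The point holds. Five batteries with dozens of variables are all primary, no lead variable, time point or contrast is fixed, and no stated procedure controls error across outcomes. If any one significant variable counted as success, the false-positive chance would be about 23% for 5 independent tests and up to about 96% for about 64. For 64 equally correlated tests it falls to about 67% at correlation 0.5 and 21% at 0.9, so it stays at least four times the nominal level over the assumed range. These figures rest on my count, on no effect in any variable, and on assumed correlations.

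Two smaller defects belong to the same list. BMI is both demographic and primary. Ankle strength is primary in the abstract, but Methods describes only a knee test. A reader might infer that ankle strength should be deleted. The documents do not support that: the article is condensed, and the resistance programme trains ankle muscles. The two passages need reconciling.

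**What to change.** Before unblinding, amend the protocol and update the registry entry.

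1. Name and justify one primary variable, one time point and one between-arm contrast. Knee-extensor peak torque or the knee proprioception threshold at 3 months would both fit the Background, which stresses quadriceps strength and proprioception alike. The choice is the sponsor's. It should say which comparator (health education or resistance training) carries the primary claim, and which knee is analysed when disease is bilateral.
2. Alternatively, fix one variable per domain (strength, proprioception, latency, gait) and test them with Holm at overall 0.05.
3. Label all other measures secondary or exploratory.
4. Move height, weight and BMI to baseline description.
5. Reconcile the ankle-strength entry in the abstract with the strength section in Methods.
6. Recheck and restate power for the chosen endpoint and contrast, giving the model and its assumptions.

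The cost is wording and a registry update; the article reports recruitment as ongoing. Most measures lose primary status, and keeping several primaries under Holm lowers power for each, as the working shows. A single primary tested with the model behind the stated sample size keeps alpha at 0.05 and N at 120. A two-arm contrast needs its own calculation.

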**Discussion:**

Important features of this trial mainly include intervention setting, outcome measure selection, and study duration. This study is intended for estimating the effect of WBV intervention on neuromuscular control outcomes. Study results may provide evidence to support the beneficial effects of WBV exercise on the physical performance and neuromuscular control of individuals with KOA to fill the research gap on the efficacy of WBV.

**Trial registration:**

Chinese Clinical Trial Registry, ID: ChiCTR-IOR-16009234. Registered on 21 September 2016.

**Electronic supplementary material:**

The online version of this article (doi:10.1186/s13063-017-2170-6) contains supplementary material, which is available to authorized users.

## Background

Osteoarthritis (OA) is a major cause of disability in the aging population; this condition has increased in prevalence in recent years, and its consequences significantly affect society [1, 2]. In the United States in 2005, OA affected 13.9% of adults aged 25 years and older and 33.6% (about 12.4 million) of those aged 65 years and older [3]. In some regions of China, the prevalence of knee osteoarthritis (KOA) is 42.8% in women and 21.5% in men aged 60 years and older [4]. A report from the World Health Organization indicated that 80% of OA patients older than 60 years experience limited movements and 25% cannot perform major daily activities [5]. Hip and knee OA is a leading cause of global disability; this condition was ranked the 11th highest contributor to global disability and the 38th highest in disability-adjusted life years among 291 conditions [6].

About 13% of women and 10% of men aged 60 years and older suffer from symptomatic KOA [2]. Individuals with KOA often report joint pains, stiffness, and impaired body functions such as muscle strength, proprioception, and joint stability [7]. No cure for KOA currently exists. The management of KOA is broadly divided into nonpharmacological, pharmacological, and surgical treatments [8]. The optimal management of patients with KOA requires a combination of pharmacological and nonpharmacological treatments, and even sometimes surgical treatment [9]. The American College of Rheumatology recommends that aerobic and/or resistance land-based exercise, aquatic exercise, weight loss, Tai Chi, traditional Chinese acupuncture, patient education, and using wedged insoles are effective nonpharmacological treatments for patients with KOA [9].

Exercise and physical therapies are recommended for the nonpharmacological management of KOA; these treatments may be important alternatives for bridging the gap between the disease onset and a final operative intervention [10, 11]. Recent studies have considered whole body vibration (WBV) exercise as an efficient and alternative treatment for individuals with KOA [12, 13]. WBV exercise is easy and safe to perform. In WBV exercise, vibration signals are delivered through a vibratory platform or chair to expose a larger part of the body to the stimulation [14]. WBV exercise provides an amplitude of displacement (0.7–14 mm) and a mechanical oscillation of a specific frequency (0.5–80 Hz) [15, 16]. WBV exercise reduces pain and improves physical functions in patients with KOA; hence, it is suggested that it be included in rehabilitation programs [12, 13].

Neuromuscular function is the ability of the nervous system to produce muscular activities and maintain body movements through integration of the afferent signals from peripheral neurons and control of the efferent signals [17]. Neuromuscular function contributes to the development and/or progression of KOA [18]. Individuals with KOA exhibit impaired proprioceptive function of the affected joint compared with age-matched controls [19]. A narrative review reported that the impairment of proprioception might play a vital but undefined role in KOA, and the effect of exercise therapy on proprioceptive accuracy in patients with KOA is required [19]. The quadriceps femoris muscle is significantly impaired in patients with KOA; both activation deficit and atrophy contribute to quadriceps weakness [20]. Muscle impairments in patients with KOA also involve hamstrings and hip muscles [20]. Therefore, improvement of the proprioceptive function and quadriceps strength is important for KOA management. Various studies have reported that WBV exercise improves the neuromuscular function of healthy individuals, patients with neurological disorders, and even older patients with limited exercise options [21, 22]. WBV exercise improves the muscle strength, power, joint proprioception, balance, and flexibility of sedentary and older individuals [23]. In particular, WBV exercise improves quadriceps strength [24, 25]. During WBV exercise, vibrations are transmitted to the body and stimulate the primary ending of the muscle spindles, thereby activating σ-motor neurons, which cause muscle contractions similar to the tonic vibration reflex [26]. Thus, WBV exercise may be used to increase physical functions, reduce pain, and improve neuromuscular function.

Previous studies on WBV exercise for individuals with KOA focused on pain relief and physical function maintenance/improvement [12, 13]. As mentioned above, neuromuscular function is an important contributor to the development and/or progression of KOA. WBV exercise improves neuromuscular function in healthy individuals and even in patients with neurological disorders. However, limited studies have investigated the effects of WBV exercise on the neuromuscular function of individuals with KOA. Trans et al. [26] found that an 8-week WBV exercise program improves the knee extension isometric strength and threshold for the detection of passive knee extension but not the self-reported knee pain and physical function in female patients with KOA. However, they did not evaluate the physical function in daily life related to KOA (i.e., range of joint motion). The passive proprioceptive test on the knee only measured knee extension, and the neuromuscular response of the lower extremity muscle and joint biomechanics were not measured. Clearly, the effects of WBV exercise on neuromuscular function, joint biomechanics, and physical functioning in the daily life of individuals with KOA must be investigated further to understand the clinical effects and relevant mechanism of the treatment. Accordingly, the present study attempts to investigate the effects of WBV intervention on knee pain and range of joint motion and to evaluate the joint biomechanics, daily physical functions, knee and ankle proprioception, and neuromuscular response of patients with KOA. We will conduct a prospective, single-blind randomized controlled trial to investigate the efficacy of a 12-week WBV program compared with lower extremity resistance training (RT) and health education on comprehensive outcomes in individuals with KOA. The results of this study will determine the effectiveness of, and provide scientific evidence for, WBV training in individuals with KOA.

